## Abstract

**Background:**

One in three patients with psoriasis will develop psoriatic arthritis (PsA). If left untreated, this can lead to pain, impaired function, and irreversible joint damage. Timely recognition and referral to a rheumatologist are therefore key. However, current methods used to screen patients with psoriasis for those who might benefit from referral to a rheumatologist are not performing well enough.

**Objective:**

The Discovery of Arthritis in Psoriasis Patients for Early Rheumatological Referral (DAPPER) study is designed to determine the prevalence of PsA in a psoriasis population and to find parameters that can be used to develop a new or enhance an existing instrument for a rheumatological referral.

**Methods:**

DAPPER is a longitudinal observational study with a 1-year follow-up. Patients with psoriasis (N=300) who are treated at an outpatient dermatological clinic will be screened extensively for signs and symptoms of PsA by a trained rheumatologist. If there is clinical suspicion of PsA and the patient is not yet treated by a rheumatologist, referral to the Department of Rheumatology will follow for confirmation of the diagnosis and further care. After 1 year, data on changes in quality of life and PsA and psoriasis disease activity will be collected from the referred patients. The screening visit will be used to gather demographical and medical data, which can later be used to develop the aforementioned screening instrument.

**Results:**

Inclusion started in June 2019 and finished in June 2021. Follow-up with newly discovered patients with PsA is ongoing.

**Conclusions:**

The DAPPER study is specifically designed to improve the detection of existing PsA in a dermatologic outpatient setting. Although internal validity will be tested, external validity will have to be checked using a second validation cohort. To predict the development of PsA in the future, longitudinal/prospective data collection is required and will be performed in a follow-up study (DAPPER-i).

**Trial Registration:**

Dutch Trial Register NTR7604; https://www.trialregister.nl/trial/7397

**International Registered Report Identifier (IRRID):**

DERR1-10.2196/31647

## Introduction

Psoriasis is a common immune-mediated skin disease. Besides skin and nails, psoriatic disease can also involve several other domains such as the entheses and the peripheral as well as the axial joints. This involvement of the musculoskeletal system defines psoriatic arthritis (PsA). PsA is an inflammatory rheumatic disease, related to other spondyloarthritides such as reactive arthritis, ankylosing spondylitis, or inflammatory bowel disease–associated arthritis. About one in three patients with psoriasis in the dermatological outpatient clinic will eventually develop PsA [1,2]. The order and amount of domains involved display a large variation in different patients and at different time points [3]. However, the musculoskeletal symptoms often develop after the disease shows itself in skin or nails. On average, the lag time between skin and joint involvement is 10 years [4].

When joints or entheses become inflamed, these can cause significant pain and have a large impact on the quality of life [5]. Moreover, ongoing inflammation of joints can lead to irreversible joint damage and disability [6,7]. Early and adequate treatment of arthritis leads to an improvement of both joint function and quality of life [8,9]. Therefore, it is important to recognize and treat patients with concomitant arthritis as soon as possible.

The treatment strategies for psoriasis and PsA show considerable overlap [10,11]. Several pharmacological options are effective and recommended to treat both skin and joints. These encompass, for example, conventional systemic drugs such as methotrexate and several biological drugs such as tumor necrosis factor alpha inhibitors and interleukin-17 inhibitors. However, some options are only available for one of these disease entities. This may be because of the delivery mode (eg, topical application of creams for psoriasis or local injections of corticosteroids for PsA) or because of a difference in efficacy in controlling either joint or skin disease (eg, retinoids for psoriasis and leflunomide for PsA). This could mean that the therapy a patient uses for their skin can also be effective for their musculoskeletal complaints.

To ensure early adequate treatment and prevent (irreversible) morbidity, early recognition and early referral to a rheumatologist are key. The combined guidelines of the American Association of Dermatologist and the National Psoriasis Foundation calls screening of patients with psoriasis for PsA “essential at each visit” [12]. However, recognition of inflammatory joint complaints is not part of the dermatological scope. In addition, due to a large prevalence of noninflammatory joint complaints, referral of all patients with musculoskeletal pain is considered an unnecessary drain of resources. Therefore, about one in three patients with PsA remain unrecognized in the dermatological clinic [1] and are at risk for irreversible damage.

To aid the recognition of PsA by dermatologists, several screening questionnaires have been developed [13-16]. Most of these are based on multiple patient-reported signs or symptoms and result in a cumulative score. Referral to a rheumatologist is recommended when a certain score is reached. Unfortunately, testing of these questionnaires in new cohorts often had disappointing results [17,18]. The long average lag time between psoriasis and PsA also necessitates repeated use of a screening tool on a regular basis. However, none of the questionnaires were validated for reuse. These are all clues that current referral strategies are inadequate.

By screening a psoriasis population for the presence of concomitant PsA, we want to determine the prevalence of (undiscovered) PsA in this group. During this screening visit, we will gather data about several clinical characteristics. These will be used to ultimately develop a new or enhance an existing instrument for rheumatologic referral. This study is therefore called the Discovery of Arthritis in Psoriasis Patients for Early Rheumatology Referral (DAPPER).

## Methods

### Aim

The aim of this study is to determine the number of patients with (untreated) PsA in a group of psoriasis patients in a dermatological outpatient clinic. Furthermore, we want to optimize the detection of PsA in patients with psoriasis in a dermatological outpatient clinic. For this purpose, we defined the following research questions.

The primary objective is to determine the prevalence of very early, newly-discovered, and known PsA in a cohort of patients with psoriasis treated at a dermatology outpatient clinic.

The secondary objectives include determining if, in newly diagnosed patients with PsA, PsA disease activity and quality of life differ before and 1 year after rheumatological referral in case of PsA; discovering clinical parameters that are associated with the presence of PsA in a cohort of patients with psoriasis; and using the aforementioned parameters to develop a new or enhance an existing screening tool for concomitant PsA in patients with psoriasis.

### Design

The DAPPER study is a monocenter observational study with a follow-up of 1 year. We will examine 300 patients stratified 1:1:1 according to current dermatological treatment (topical or UV therapy only, conventional systemic medication but no biologicals, biological therapy).

The initial screening at the dermatology department will include a 68 tender joint count, 66 swollen joint count, a dactylitis count (0-20), and enthesitis scores (Leeds Enthesitis Index [LEI] [19] and the enthesitis score of the Spondyloarthritis Research Consortium of Canada [SPARCC] [20]). Inflammatory back pain will be assessed via the criteria of the Assessment of Spondyloarthritis International Society [21]. At this study visit, no laboratory tests or imaging will be performed for diagnostic purposes.

To investigate possible identifying characteristics or confounders for the detection of PsA, the study visit will also be used to gather demographical data (comorbidity, treatment data, and clinical characteristics of the skin). An example of the interview guide used is shown in Multimedia Appendix 1.

#### Referral and Referral Criteria

If there is a clinical suspicion of PsA in the study visit according to the study physician (trained rheumatologist), the patient will be referred to the Department of Rheumatology. Referral to a rheumatologist will be at the discretion of the investigator. A patient will be referred when not under current rheumatological care and when meeting one of the following criteria: one or more swollen joints, clinical evidence of inflammatory enthesitis, and/or inflammatory back pain. Other reasons to suspect PsA can also give rise to referral (eg, restricted movement in a joint or prolonged morning stiffness). From there on, these patients will be investigated and treated as in regular PsA care. This will include confirmation of the diagnosis with additional laboratory tests and imaging, and treat-to-target via the Psoriatic Arthritis Disease Activity Score (PASDAS) [22].

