### Outcome Measures

The primary outcome measure will be the percentage of investigated patients with the diagnosis of PsA. This diagnosis will be accepted if it was confirmed by a rheumatologist in correspondence. Fulfillment of Classification Criteria for Psoriatic Arthritis (CASPAR) is not required [23]. After 1 year, patient files of the referred patients will be checked to confirm the diagnosis. If the suspicion of active PsA is confirmed, treatment changes and their effect on disease activity will be noted. Alternatively, the other rheumatological diagnosis will be noted.

In the referred patients with PsA, HR-QoL will be assessed via two disease-specific questionnaires at referral and 1 year thereafter. Skin-related impact will be explored via the Dermatological Life Quality Index (DLQI) [24]. Joint-related impact will be explored via the Psoriatic Arthritis Impact of Disease (PsAID) [25].

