### Outcome Variables

#### Prevalence of PsA

To ascertain the presence of PsA, we will ask the patient about joint and enthesis complaints (location, pattern, and intensity), morning stiffness (duration), and whether or not they ever had a diagnosis of arthritis. For confirmation of arthritis, dactylitis, or enthesitis, we will perform joint counts (swollen, tender, and dactylitis) and enthesitis indices (LEI and SPARCC). After referral, the diagnosis of PsA or alternative diagnosis will be retrieved from (the correspondence gathered in) the electronic patient file.

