#### Possible Identifying Characteristics for the Presence of PsA in Psoriasis

We will gather information about demographic variables, comorbidity, intoxications, and family history. Family history and comorbidity will be targeted at diseases that are associated with spondyloarthritis, such as uveitis, psoriasis, and inflammatory bowel disease. Next to that, the Charlson Comorbidity Index [26] and Functional Comorbidity Index [27] will be used to evaluate a total comorbidity burden. Data about comorbidity specifically associated with either psoriasis or PsA (eg, hepatic [28], psychological [29], and cardiovascular [30] diseases) will be added. In addition, current and previous treatment for either PsA or psoriasis will be noted. Severity and location of psoriasis (via Psoriasis Area and Severity Index [31] and body surface amount will be noted. Nail involvement will be assessed via Nail Psoriasis Severity Index [32] and Nijmegen Nail Psoriasis Activity Index Tool [33]. Three of the currently used screening questionnaires (ie, Psoriasis Epidemiology Screening Tool [PEST], Toronto Psoriatic Arthritis Screen [ToPAS], and Psoriatic Arthritis Screening and Evaluation [PASE]) will be used to collect clinical characteristics that have been previously discovered in their development [13-15].

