#### Possible Identifying Characteristics for the Presence of PsA in Psoriasis

The identifying value of various clinical markers for the presence of PsA in psoriasis will be processed as independent variables in a univariate logistic regression model. Diagnosis of PsA (yes/no) will be the dependent variable. Variables that are statistically related to the outcome (*P*≤.20 in univariate modeling) and are clinically and methodologically feasible (based on a favorable balance between prevalence in the cohort, effect size, and ease of measurement) will be selected. The subsequent selection of variables will be tested in a multivariable logistic regression model with backward stepwise selection. Sensitivity analysis will be performed by reclassifying patients with an uncertain diagnosis as cases. The number of possible independent variables will be limited based on a minimum of 10 events (PsA diagnoses) per variable. Bootstrapping will be used to assess the internal validity of the model in terms of overoptimism and shrinkage.

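### Treatment given for PsA and an earlier arthritis diagnosis are not barred as predictors of PsA, although patients with known PsA stay in the modelled cohort

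*Protocol article*

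**What the plan says.** All references are to the protocol article.

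- **Candidate characteristics.** Under *Outcome Variables, Possible Identifying Characteristics for the Presence of PsA in Psoriasis*, the list covers demographics, comorbidity, family history, skin and nail scores, and content from three screening questionnaires. It also states: "In addition, current and previous treatment for either PsA or psoriasis will be noted". *Design* says that treatment data are gathered to look for identifying characteristics or confounders.
- **Cohort.** *Participants* does not exclude patients with an earlier PsA diagnosis or under a rheumatologist's treatment. The primary objective counts known PsA.
- **Ascertainment.** *Prevalence of PsA* records, among other things, "morning stiffness (duration), and whether or not they ever had a diagnosis of arthritis". The outcome is the rheumatologist's diagnosis: "This diagnosis will be accepted if it was confirmed by a rheumatologist in correspondence".
- **Referral.** The firm criteria are "one or more swollen joints, clinical evidence of inflammatory enthesitis, and/or inflammatory back pain". Beyond these: "Other reasons to suspect PsA can also give rise to referral (eg, restricted movement in a joint or prolonged morning stiffness". Laboratory tests and imaging follow referral only.
- **Model.** The *Statistics* section with the same heading as the candidate list takes diagnosis of PsA (yes/no) as the dependent variable. It keeps variables at P≤.20 that are feasible, "based on a favorable balance between prevalence in the cohort, effect size, and ease of measurement", then applies backward selection. Bootstrapping is the internal check.

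**The concern.** A patient is treated for PsA because someone has already diagnosed it, and a report of an earlier arthritis diagnosis largely restates the outcome. With known cases counted as events, such items separate cases from non-cases very well and tell a dermatologist nothing about a patient not yet diagnosed. The stated filter does not ask whether a variable follows from the diagnosis. Two of its three feasibility considerations, effect size and ease of measurement, speak for keeping such a variable.

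Bootstrapping estimates how much a model has overfitted its sample. It redraws patients with the same labels and the same predictors, so a link between predictor and label that is built into the data is reproduced in every resample. The reported performance would then describe mainly recognition of known PsA, while the stated purpose is to detect concomitant PsA for referral.

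A second, weaker link concerns symptoms. A patient who is not under rheumatological care and is not referred gets no laboratory tests or imaging. That patient's non-PsA label rests partly on the absence of the signs that prompt referral. If questionnaire items covering those symptoms enter the model, their association with the label may be somewhat too strong.

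**Working it through.** **The plan's own figures.** 50/0.30 = 166.7, so 167 patients; 100/0.20 = 500. With 300 patients, 300 × 0.20 = 60 and 300 × 0.30 = 90 cases, hence 6 to 9 variables at 10 events each. These reproduce, and this point changes none of them.

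**1. PsA treatment as a single predictor**

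Inputs:
- Share of PsA already recognised: 2/3. The *Introduction* says about one in three remain unrecognised.
- Share of recognised patients with treatment recorded as given for PsA: 50-90% (assumed).
- Specificity: about 1 (assumed, because treatment for PsA presupposes the diagnosis).

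For a yes/no item, AUC = (sensitivity + specificity)/2.

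- At 50%: sensitivity = 2/3 × 0.5 = 0.33, AUC = (0.33 + 1)/2 = 0.67.
- At 90%: sensitivity = 2/3 × 0.9 = 0.60, AUC = (0.60 + 1)/2 = 0.80.
- In undiagnosed patients: sensitivity is near 0, so AUC is near 0.50.

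**2. Whether bootstrapping would show it**

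A simulation used N = 300, 25% prevalence, 2/3 of PsA known, 90% of known cases treated for PsA, and a few other markers of modest strength. Undiagnosed patients without a referral sign were labelled non-PsA, and 0 to 40% of sign-positive non-PsA patients were labelled PsA. Only 2/3 and N come from the document directly; 25% is the middle of its prevalence range, and the rest is assumed. The referral sign was left out of the predictors.

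| Predictors | Bootstrap-corrected AUC, whole cohort | True AUC in undiagnosed patients |
|---|---|---|
| Other markers only | 0.60-0.68 | 0.67 |
| Other markers + PsA treatment | 0.76-0.89 | 0.62-0.66 |

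With PsA treatment in the model, the bootstrap took off only 0.02 to 0.03 (for example 0.906 to 0.890). The remaining gap to undiagnosed patients was 0.14 to 0.23 (for example 0.890 − 0.656 = 0.234). Without it, performance was not overstated to any material degree.

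**3. A symptom that also prompts referral**

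All sign and diagnosis probabilities here are assumed. The sign has sensitivity 0.60 and specificity 0.70, so the true odds ratio is (0.60/0.40)/(0.30/0.70) = 3.5. Known cases (2/3) keep their diagnosis whether or not the sign is present. Among undiagnosed PsA patients, the diagnosis is made with probability a (sign present) or b (sign absent). Among non-PsA patients, it is made falsely with probability c or d.

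Worst scenario (a = 98%, b = 50%, c = 10%, d = 0.5%), 20% prevalence, 300 patients. There are 40 known cases (24 with the sign), 20 undiagnosed cases (12 with the sign) and 240 non-cases (72 with the sign):
- Labelled PsA, sign present: 24 + 12 × 0.98 + 72 × 0.10 = 42.96
- Labelled PsA, sign absent: 16 + 8 × 0.50 + 168 × 0.005 = 20.84
- Labelled non-PsA, sign present: 12 × 0.02 + 72 × 0.90 = 65.04
- Labelled non-PsA, sign absent: 8 × 0.50 + 168 × 0.995 = 171.16
- Apparent odds ratio: (42.96 × 171.16)/(20.84 × 65.04) = 5.4
- Apparent sensitivity: 42.96/63.80 = 0.67, against 0.60

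| a, b, c, d | Odds ratio at 20% prevalence | Odds ratio at 30% prevalence |
|---|---|---|
| 97%, 85%, 4%, 1% | 3.8 | 3.8 |
| 97%, 70%, 6%, 0.5% | 4.4 | 4.3 |
| 98%, 50%, 10%, 0.5% | 5.4 | 5.2 |

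**The case against.** **The article does not say that PsA treatment will be a predictor.** It says that treatment will be noted, mentions confounders as well as identifying characteristics, and leaves room for judgement on feasibility. The exact candidate list may be in a fuller document. This stands as far as it goes: the inflation is conditional on the item being used. But the article places the item under the heading that the model section repeats, and it gives a selection rule that would keep it. Correcting that rule is not a request for missing detail.

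**A reader might infer that the whole model is circular and relearns the referral rule.** The document does not support that. Joint counts, enthesitis scores, inflammatory back pain and restricted movement serve screening, referral and ascertainment; none is listed as a candidate. Overlap through the questionnaires depends on their items, which are not shown. All 300 patients are examined by a trained rheumatologist. Referral is not the outcome, since a rheumatologist must confirm the diagnosis, with laboratory tests, imaging and a file check after one year. The *Discussion* states that the aim is detection, so current symptoms are legitimate predictors.

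**A reader might also expect a larger symptom effect.** With no known cases and 10% prevalence, the three scenarios give odds ratios of 4.1, 6.0 and 9.8. The plan does not fit that model: it uses the whole cohort, where known diagnoses do not depend on the study visit. Those figures resemble a cohort restricted to undiagnosed patients (at 25% prevalence, 25 undiagnosed cases among 250), so a subgroup result is not free of this effect either.

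**Comparing models with and without the symptom items would not measure the bias.** The assumed sign, labelled without error, has an AUC of (0.60 + 0.70)/2 = 0.65 against 0.50 without it. That is a gap of 0.15 with no bias at all.

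**External validation is already required before use.** True, but it comes after the model is built and does not remove an unsuitable candidate. Nor does the document attribute the earlier questionnaires' disappointing results to this mechanism; it points to few cases and to where patients were recruited.

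**Conclusion.** The point holds in a limited form. As written, the selection rule admits and favours treatment for PsA. It has no bar on an earlier arthritis diagnosis, which is recorded for ascertainment though not listed as a candidate. If PsA treatment is used, it alone can contribute an AUC of 0.67-0.80 in the whole cohort with almost no value in undiagnosed patients, and the planned bootstrap would not reveal this. That range rests on two thirds of PsA being known (from the document), 50-90% of known cases being treated for it (assumed) and specificity near 1 (assumed).

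The symptom effect is secondary. It arises only if questionnaire items covering referral symptoms enter the model. Its illustrated size in the whole cohort, 3.5 appearing as about 3.8 to 5.4, depends on assumed diagnosis probabilities that the document neither gives nor contradicts. The prevalence estimate and the study size are not affected.

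**What to change.** In *Statistics, Possible Identifying Characteristics for the Presence of PsA in Psoriasis*:

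1. State that treatment given for PsA, and any item asking about an earlier arthritis or PsA diagnosis, are not candidate predictors.
2. Report the model's optimism-corrected performance also in patients without known PsA at the study visit, next to the whole-cohort result.
3. State as a limitation that non-referred patients are labelled non-PsA partly because the referral signs were absent, so the performance of symptom items may be optimistic, in the subgroup as well. Do not present a performance gap between models with and without these items as the size of that effect.

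This needs wording and one further summary of data already collected, with no new patients or assessors. The reported performance will probably be less favourable. The subgroup estimate will be imprecise: with 60 to 90 cases and one third unrecognised, it rests on about 20 to 30 cases (60/3 to 90/3). At 10 events per variable that would support only 2 to 3 predictors, so the subgroup should serve to evaluate the model and not to rebuild it.

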#### Follow-up

Only those patients with a newly discovered PsA, as confirmed by a rheumatologist after referral, will be approached for follow-up after 1 year. At that moment, changes in treatment, disease activity, and health-related quality of life (HR-QoL) will be noted.

